### Definition of high-risk threshold

All jaundiced infants with elevated TSB, defined as 3 mg/dl below the level recommended by the American Academy of Pediatrics (AAP)
[27] for PT in high-risk infants, will be considered at high risk. The high-risk classification category of the AAP guideline was selected because laboratory evaluation for hemolysis will not be consistently available during the study, and Nigerian infants are known to be at higher risk for severe NNJ secondary to glucose-6-phosphate dehydrogenase (G6PD) deficiency
[28]. This TSB level was chosen also because many hospitals begin PT about 2 to 3 mg/dl below the current level in the United States, due to the severity of NNJ and the sub-optimal PT treatment in most locations in Nigeria.

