#### Evaluation criteria

Change in TSB level per hour of therapy defined as a binary variable. The TSB level will be measured immediately before beginning therapy on a given day and immediately after therapy is completed that day, and the change in bilirubin level in mg/dl per hour of therapy will be calculated. For infants who are less than 72 hours old in the morning, the treatment will be judged efficacious if the bilirubin level rises more slowly than 0.2 mg/dl per hour of therapy that day. For infants who are more than 72 hours old, the treatment will be judged efficacious if the bilirubin level falls. Efficacy will be evaluated only for days in which the treatment was deemed safe (that is, when the infant did not have to be removed from PT due to a need for physician treatment for sunburn or dehydration, persistent temperature instability defined as two or more episodes of temperatures <35.0 or >39.0°C, or failure to return to normothermia (defined as 35.5 to 38.0°C) within 1 hour of being removed from PT). The average efficacy of each type of PT, defined as the proportion of safe days where a given therapy was used in which the therapy was efficacious, will be compared. FS-PT will be considered at least as efficacious as CPT if the average efficacy on days where FS-PT was used is no worse than 10% less than the average efficacy on days where CPT was used.

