### Sample size

The minimum sample size was estimated using the following assumptions: 1) the average efficacy of CPT is 80%; 2) the average efficacy of FS-PT is 80%; 3) there will be the same number of infants assigned to both groups; 4) the delta value is 10% - that is, we want to demonstrate that FS-PT is no more than 10% worse than CPT; and 5) 80% power, one-sided alpha = 0.025.

Under these assumptions, a total of 504 days, or 252 days in each treatment group, will be required. This calculation gives the required number of treatment days that are evaluable for efficacy. Since efficacy will be evaluated only for days in which the treatment was deemed safe, the sample size was increased to account for the possibility that the proportion of safe days might be as low as 90%. Assuming that the safety of both FS-PT and CPT is 90%, a sample size of 560 total days is required. Assuming that a typical course of treatment lasts 1 day, both for FS-PT and CPT, then 560 infants, or 280 infants in each group, will be required. Anticipating up to 10% loss due to rainy days (in the FS-PT group), delisting of infants by parents or guardians, or missing data (in both groups), we will enroll 616 infants, or 308 infants in each group. From our year 1 data in the preceding observational study only 66% of the 826 infants referred for elevated TcB had significant elevated TSB levels, hence 915 infants or more will be enrolled for stage 1 bilirubin estimation until the total requirement of 560 treatment days is reached (Figure 
2).

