### Laboratory testing procedures

#### *G*lucose-6-phosphate dehydrogenase

Because of the high prevalence of G6PD deficiency in our study population, enrolled infants will be routinely screened for this condition using simple and inexpensive supplies. The method will be based on the fluorescent blood spot originally developed by Beutler and colleagues
[29]. This test has been considered a standard method of G6PD screening especially in resource-poor settings, since inexpensive reagents and materials can be used.

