### Data collection and analysis

Data will be collected on paper case report forms and entered via a web interface into a secure database. The study data will be collected and managed using REDCap (Research Electronic Data Capture) electronic data capture tools hosted at the University of Minnesota’s Academic Health Center. REDCap is a secure, web-based application designed to support data capture for research studies, providing: 1) an intuitive interface for validated data entry; 2) audit trails for tracking data manipulation and export procedures; 3) automated export procedures for seamless data downloads to common statistical packages; and 4) procedures for importing data from external sources.

Demographic data will be summarized and compared between the treatment and control groups using appropriate methods, such as Pearson’s chi-square test for categorical variables and two-sample t-tests for continuous variables. The primary objective is to compare the efficacy of FS-PT and CPT. A 95% exact binomial confidence interval for the true difference in efficacy between the FS-PT treated and CPT control groups will be calculated. FS-PT will be deemed non-inferior to CPT if the calculated confidence interval does not extend more than 10% below the equivalence point.

We plan to conduct three distinct analyses: an intent-to-treat analysis based on the assigned treatment for each enrolled infant, an as-treated analysis based on the actual treatment received on a given day and a per-protocol analysis including only enrolled infants who received the assigned treatment on all of their treatment days.

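### The primary non-inferiority interval is valid without adjustment, but it could gain precision by using the pre-randomisation TSB and the 72-hour age class

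*Protocol article*

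**What the plan says.** Under Data collection and analysis, the article sets the primary comparison: "A 95% exact binomial confidence interval for the true difference in efficacy between the FS-PT treated and CPT control groups will be calculated". Non-inferiority is declared if that interval does not reach more than 10% below equality. No covariate, stratified interval or model is named. Demographic data are only compared between arms, with chi-square and t-tests. Three analyses are listed (intent-to-treat, as-treated, per-protocol).

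The outcome, under Evaluation criteria, is a success or failure for each safe treatment day, built from two bilirubin readings: "The TSB level will be measured immediately before beginning therapy on a given day and immediately after therapy is completed that day". Success means a rise slower than 0.2 mg/dl per hour for infants under 72 hours old that morning, and a fall for older infants.

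Subject recruitment, Randomization scheme and Pre-treatment (stage 1) all require a TSB before allocation, because it determines whether the infant is randomised. Randomisation uses variable blocks, and no stratification factor is named. On G6PD, the article says that "enrolled infants will be routinely screened for this condition using simple and inexpensive supplies", and gives as background that "Nigerian infants are known to be at higher risk for severe NNJ secondary to glucose-6-phosphate dehydrogenase (G6PD) deficiency". It does not say when G6PD results become available.

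**The concern.** Each day's result comes from a change in TSB, with a success rule that depends on age. Starting TSB and age class may therefore help to predict whether a day counts as efficacious. If they do, a crude difference leaves that explained variation in the standard error, and neither the randomisation scheme nor the baseline significance tests removes it. A standardised risk difference would estimate the same quantity against the same margin with a narrower interval. What is at stake is some ability to show non-inferiority, using data that the trial already collects.

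**Working it through.** **Inputs (Sample size section).** Efficacy is 80% in both arms. The margin is absolute: "we want to demonstrate that FS-PT is no more than 10% worse than CPT". The error rates are "80% power, one-sided alpha = 0.025". Allocation is equal, with 252 evaluable days per arm. The article gives no association between any baseline variable and daily efficacy, so that input is an assumption, shown as a range.

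**Step 1: the plan's own figure.** n per arm = [0.8×0.2 + 0.8×0.2] × (1.960 + 0.842)² / 0.10² = 0.32 × 7.849 / 0.01 = 251.2, rounded up to 252, or 504 in total. This matches. Dividing 504 by 0.90 gives 560, and 560 × 1.10 = 616, also as stated. The sample size therefore rests on the same unadjusted comparison as the analysis.

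**Step 2: power of the crude analysis.** SE = √(0.32/252) = 0.03563. Power = Φ(0.10/0.03563 − 1.960) = Φ(0.846) = 80.1%. This treats days as independent, in line with the plan's assumption of a one-day course.

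**Step 3: effect of adjustment.** If baseline covariates explain a share R² of the outcome variance, the variance of the risk difference is multiplied by about (1 − R²). Power is then Φ(0.10/[0.03563 × √(1 − R²)] − 1.960).

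| Assumed R² | Power at 252 per arm | 95% half-width (points) | n per arm for 80% power |
|---|---|---|---|
| 0 | 80.1% | 6.98 | 252 |
| 0.05 | 82.1% | 6.81 | 239 |
| 0.10 | 84.1% | 6.63 | 227 |
| 0.20 | 88.1% | 6.25 | 201 |

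To judge which R² is plausible, take one standardised covariate in a logistic model with 80% marginal success. An odds ratio per SD of 1.25 gives R² 0.008 and power 80.4%. An odds ratio of 1.5 gives 0.026 and 81.1%, 2 gives 0.071 and 82.9%, and 3 gives 0.156 and 86.3%.

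**Step 4: is the crude analysis valid?** One-sided error was simulated at the margin (80% versus 70%, 252 per arm, 40,000 runs, Wald interval rather than the exact one). It was 2.5%, 2.5% and 2.6% for covariate odds ratios of 1, 2 and 3 per SD. Chance imbalance does not inflate error.

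**Step 5: size of chance imbalance.** The difference in covariate means between arms has SD √(2/252) = 0.089 covariate SDs. An imbalance of one such SD moves the estimated risk difference by 0.6 points (odds ratio 1.5) to 1.3 points (odds ratio 3). An imbalance of 1.96 SDs moves it by 1.1 to 2.6 points. The 7-point half-width already allows for this variation.

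**Step 6: if efficacy is higher than assumed.** The observational study reports 94% (164/175). With 94% in both arms, SE = √(2×0.94×0.06/252) = 0.0212 and crude power is about 99.7%. With 90% in both arms, SE = √(0.18/252) = 0.0267 and power is about 96%. Adjustment then has little left to add.

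**The case against.** The strongest reply is that nothing here is wrong. Analysis and sample size match, the crude interval keeps its error rate, and a supporting adjusted analysis may sit in an analysis plan that is not shown. That stands, and it limits this point to a recommendation.

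The expected benefit is also uncertain. Entry criteria narrow the TSB range, since infants must be above a lower threshold and below exchange-transfusion criteria. The pre-randomisation TSB is not the morning baseline for later treatment days, and the article does not establish that it is the same sample on day 1. G6PD is cited as a risk for severe jaundice, not as a predictor of daily response. Its timing is not given, and the Definition of high-risk threshold section warns that laboratory work-up for haemolysis will not be consistently available. These points shrink the likely gain and make G6PD an optional covariate. They do not show that adjusting for TSB and age class would be wrong.

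Three stronger readings are tempting, and the documents support none of them:

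- **Chance imbalance biases the result.** Under randomisation the crude difference is unbiased, and its interval covers chance imbalance (Step 4).
- **The trial is underpowered for lack of adjustment.** The stated power is reached without it, and the only empirical efficacy figure, from a single-arm study that may not transfer, suggests reserve.
- **The gain is large.** A correlation of 0.5 (R² 0.25) would give 90% power, but no passage supports that value. In simulation, logistic slopes of 1.5 and 2 gave correlations of 0.45 and 0.52, so 0.5 needs an odds ratio of roughly 4.5 to 7.4 per SD.

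**Conclusion.** The point holds as an efficiency improvement. The crude primary interval is valid and has its stated 80% power under the plan's assumptions. It forgoes precision only to the extent that pre-randomisation TSB and age class predict daily efficacy. The gain at 252 per arm and 80% efficacy is about 2 points of power at R² 0.05, 4 at 0.10 and 8 at 0.20, and close to nothing near zero. For a single covariate with an odds ratio of up to 2 per SD, it is at most about 3 points. These figures assume one evaluable day per infant, 80% efficacy in both arms and the usual large-sample variance reduction. They also set aside the restriction of the outcome to safe days.

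**What to change.** In Data collection and analysis, specify before outcomes are compared between arms that the intent-to-treat comparison uses a standardised (marginal) risk difference. Obtain it from a logistic model with:

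- treatment;
- the pre-randomisation TSB that qualified the infant, expressed relative to the AAP threshold;
- age class at randomisation (under or over 72 hours).

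Do not use later morning TSB values, which treatment can affect. Add G6PD status only where the result cannot depend on treatment, with a category for missing results so that no infant is dropped.

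Give 95% limits from an infant-level robust variance or an infant-level bootstrap, which also allows for infants with more than one day. Keep the 10-point margin unchanged and report the crude exact interval as a sensitivity analysis.

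The cost is wording only, with no new data or infants and no change to the sample size. The downside is that the main interval becomes large-sample and model-assisted rather than exact. That is acceptable at about 250 per arm with 80% success, and the crude interval remains as a check. Because the trial is unblinded and recruitment was under way at publication, the change should be dated and made without sight of results by arm.

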### Randomization scheme

Enrolled infants with elevated TSB (defined as 3 mg/dl below the level recommended by the AAP to begin PT in high-risk infants) will be randomly assigned to receive FS-PT or CPT. A block randomization procedure with variable block sizes will be used to maximize unpredictability. The randomization assignments of FS-PT or CPT will be printed on sequentially numbered sheets of paper and enclosed in opaque, sealed, sequentially numbered envelopes. The sealed envelopes will be prepared independently by the study statistician based in the USA and transported to Nigeria by the regulatory sponsor. When an enrolled infant’s TSB level is obtained and found to be 3 mg/dl or more below the AAP threshold for high-risk infants the study nurse will request the next envelope. The envelope will be opened and both the envelope number and the treatment assignment will be recorded on the case report form. The laboratory technician responsible for measuring the serum bilirubin level will be unaware of the sequence of treatment allocation of either FS-PT or CPT for each eligible infant and will not be involved in administering PT. The study will not be blinded as it is not physically possible to blind either the participating infants or parents, nor the hospital personnel.

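### Infants are randomised but treatment days are analysed as independent, so the deciding interval is too narrow to the extent that infants contribute repeat, correlated days

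*Protocol article*

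**What the plan says.** The Randomization scheme section allocates infants: those with elevated bilirubin "will be randomly assigned to receive FS-PT or CPT". The Evaluation criteria section makes the day the unit of the primary outcome, with average efficacy "defined as the proportion of safe days where a given therapy was used in which the therapy was efficacious".

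Under Data collection and analysis, the deciding statistic is: "A 95% exact binomial confidence interval for the true difference in efficacy between the FS-PT treated and CPT control groups will be calculated". FS-PT is non-inferior if that interval does not reach more than 10% below equality. The section also plans intent-to-treat and per-protocol analyses, and "an as-treated analysis based on the actual treatment received on a given day".

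The Sample size section asks for 252 evaluable days per group, 504 in all, raised to 560 for unsafe days. It converts days to infants one for one: "Assuming that a typical course of treatment lasts 1 day, both for FS-PT and CPT". It then gives two accrual targets. One is 616 infants, 308 per group. The other is stage 1 enrolment "until the total requirement of 560 treatment days is reached".

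**The concern.** A binomial interval needs the counted days to be independent. Days from one infant share the cause of jaundice, the feeding and the course of bilirubin. The protocol itself notes a high prevalence of G6PD deficiency, a fixed trait of the infant. Positive within-infant correlation is therefore plausible.

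Repeat days are also provided for:

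- Treatment efficacy calls for a bilirubin measurement each morning and another at the end of each treatment day.
- The exit criteria count the protocol as complete only when bilirubin is no longer elevated.
- The per-protocol set is defined over all of an infant's treatment days.
- Before 72 hours of age, a sufficiently slow rise counts as success, so a successful day need not end treatment.

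The lower confidence limit decides the trial. If it lies too close to the estimate, a truly inferior FS-PT is accepted more often than the planned one-sided 2.5%.

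**Working it through.** **Inputs from the Sample size section:** efficacy 80% in both groups, margin 0.10, one-sided alpha 0.025, power 80%, 252 evaluable days per group.

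**Reproducing the plan's figure.** With independent days, SE = sqrt(2 × 0.8 × 0.2 / 252) = 0.0356. Then 0.10/0.0356 − 1.96 = 0.846, giving power of 80.1%. The formula requires 251.2, hence 252 per group. 504/0.9 = 560 also reproduces. The figure is exactly the independent-observation result and carries no allowance for clustering.

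**Assumptions not in the documents:** within-infant correlation (ICC) 0.2 to 0.5; days per infant *m* geometric, with mean 1.12, 1.5 or 2. The value 1.12 is 227/203 from the observational study described in the Background. It applies only if the 227 days there are treatment days; the wording may mean calendar days.

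**Formulas**

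- Design effect DE = 1 + (E[m²]/E[m] − 1) × ICC. For a geometric *m*, E[m²]/E[m] = 2 × mean − 1.
- One-sided error of the unclustered interval = 1 − Φ(1.96/√DE).
- Power of a correctly widened interval at 252 days per group = Φ(0.10/(0.0356 × √DE) − 1.96).

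| Mean days per infant | E[m²]/E[m] | DE (ICC 0.2 to 0.5) | One-sided error | Power, 252 days per group |
|---|---|---|---|---|
| 1 | 1.00 | 1.00 | 2.5% | 80.1% |
| 1.12 | 1.24 | 1.05 to 1.12 | 2.8% to 3.2% | 78% to 76% |
| 1.5 | 2.00 | 1.20 to 1.50 | 3.7% to 5.5% | 73% to 63% |
| 2 | 3.00 | 1.40 to 2.00 | 4.9% to 8.3% | 66% to 51% |

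**Simulation check.** Beta-binomial simulation (20,000 trials per setting, FS-PT 70% against CPT 80%, unclustered Wald interval) gave errors of 2.8% and 3.2%, 3.5% and 5.5%, and 5.1% and 8.5% for the three means above 1. With a less variable course length (1 + Poisson) and ICC 0.1 to 0.5, the simulated errors were 2.6-3.1%, 3.0-5.1% and 3.5-7.0%. The direction is stable; the size depends on the assumptions.

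**Power under the other accrual rule.** If 308 infants per group are enrolled, longer courses add days. Applying the plan's 10% loss and 90% safe days, 308 × 0.9 × 0.9 = 249.5 evaluable days per group at one day per infant. Dividing by the design effects above:

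- mean 1.5: 249.5 × 1.5 = 374 days; 374/1.20 = 312 down to 374/1.50 = 249 effective days
- mean 2: 249.5 × 2 = 499 days; 499/1.40 = 356 down to 499/2.00 = 249 effective days

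At 249.5 effective days, SE = sqrt(0.32/249.5) = 0.0358 and 0.10/0.0358 − 1.96 = 0.83, so power is about 80%. The losses in the last column of the table therefore belong to the 560-day stop alone.

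**The case against.** The strongest reply is that the plan expects one day per infant. If every infant gave exactly one evaluable day, the design effect would be 1 and both 2.5% and 80% would hold. A reader might infer from the unit mismatch that both figures fail outright. The documents do not support that. They support a conditional statement: the interval is too narrow to the extent that repeat days occur and are positively correlated. A typical course of 1 day is not a rule of one day per infant, however, and no such rule is given.

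Several further points stand in whole or part.

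- **The larger errors rest on assumed inputs.** Means of 1.5 and 2 days and all the correlations are assumptions. The one course length that might be drawn from the documents, 1.12, gives a small excess. The pilot also reports efficacy in 164 of 175 infants, a count per infant. The Treatment duration section limits bilirubin kinetics to infants with at least 5 hours of therapy, which may drop some short days.
- **The error was computed for a normal-theory interval, not the exact one named.** Exact intervals tend to be conservative, and near 1.12 days this could absorb part of the excess. How much was not quantified.
- **A general loss of power cannot be claimed.** A reader might take the 560-day stop as the only accrual rule. The same section also states 616 infants, and under that target power is largely kept.
- **The as-treated overlap is not a further source of narrowness.** When one infant supplies days to both groups, positive correlation between them lowers the variance of the difference, which works against the concern.

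It may also be said that a journal article leaves variance estimation to the analysis plan. Here the article names the interval and the decision rule, so the point concerns a stated method and not an omitted detail.

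**Conclusion.** The point holds in conditional form. The named interval assumes independent days although the infant is randomised and may contribute several. With any positive within-infant correlation and repeat evaluable days, an interval built on independence is too narrow. Under the assumptions above, the nominal 2.5% one-sided error becomes about 3% if courses average 1.12 days, and up to 5.5% at 1.5 days or 8.3% at 2 days, before any offset from exact conservatism.

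The loss of power is a separate and weaker matter. It depends on which of the two accrual statements governs. The interval is too narrow under either, so enrolling 616 infants protects power but does not repair the error rate.

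**What to change.** **Data collection and analysis:** replace the day-level exact binomial interval with a 95% interval for the risk difference that treats the infant as the cluster. Either of these would serve:

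- GEE with identity link, independence working correlation and infant-clustered robust standard errors
- a bootstrap that resamples whole infants

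Keep the −10 point limit. With independence weighting, the estimate remains the difference in the proportions of days. Use the same approach for the intent-to-treat, per-protocol and as-treated analyses. In the as-treated analysis, keep each infant as one cluster even when its days fall in both groups.

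**Sample size:** state the recruitment target in infants, using the 616 already given, and drop the parallel stop at 560 treatment days. If the day-based stop is kept, restate power with a design effect for a declared mean number of days per infant and a declared correlation.

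**Cost:** a change of wording and possibly a restated power figure. No new data are needed, since results are already collected by infant and day. The interval becomes slightly wider; if nearly all infants contribute one day, the difference is negligible.
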